## Background

Without treatment, survival in patients with pancreatic cancer is only 4–6 months. Pancreatic resection combined with adjuvant chemotherapy can increase the median survival to 54 months in selected patients with pancreatic cancer [1]. Pancreatic resection is, however, a major abdominal operation that is associated with a 50% risk of complications [2]. Complications are associated with postoperative death and reduced long-term survival because patients with a complicated postoperative course are often unfit to receive adjuvant chemotherapy [3–5].

A common complication after pancreatic resection is pancreatic fistula, in which there is leakage of pancreatic juices into the abdominal cavity [6–9]. This complication is potentially life threatening due to its association with other complications. Leakage of pancreatic juices can lead to vessel erosion, potentially causing major bleeding. Systemic inflammation may result in sepsis, organ failure and death [8]. A postoperative pancreatic fistula that necessitates a change in postoperative management is regarded a “clinically relevant fistula” [10]. In a recent systematic review of 40 studies, clinically relevant pancreatic fistula occurred in 13% of patients after pancreatic resection [2]. A Dutch study (2005–2013) demonstrated that mortality in patients with severe pancreatic fistula remains as high as 18% [9]*.*

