### Participants

Pancreatic surgery is centralized in The Netherlands in centers performing at least 20 pancreatoduodenectomies annually. All centers performing pancreatic surgery in The Netherlands are participating in this trial. All patients undergoing all types of pancreatic resection in these centers are identified and will be recruited in this trial. There are no exclusion criteria for centers or patients (i.e. nationwide complete enumeration).

Data will be extracted from the prospective Dutch Pancreatic Cancer Audit. Additional data on clinical outcomes will be extracted prospectively through continuous systematic evaluation of patient charts using a predefined case record form. Data are stored on a central secured data capturing tool (i.e. Castor EDC) containing programmed checks for outliers. To ensure patient confidentiality, the data stored centrally will be cleaned to remove all information that could directly trace back to an individual patient, and a unique patient identifier number will be assigned to every patient. The local principal investigator will have access to the identifiable patient information. The data entered will be checked by a senior researcher. Local principal investigators are responsible for data collection. They can delegate this to the study personnel if resources are not available at the center.

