Secondary endpoints include individual components of the composite endpoint and an adapted version of the primary endpoint in which only complications are included that are deemed by the blinded adjudication committee to be directly related to a pancreatic fistula. Other secondary endpoints are: the Comprehensive Complication Index (CCI) [25] based on complications grade 3 or higher according to the Clavien-Dindo classification [19], postoperative pancreatic fistula [21], gastroenterostomy leakage, postoperative bile leakage [22], delayed gastric emptying [23], chyle leakage [26], new-onset acute pancreatitis [24], number and timing of abdominal CT scans, number, timing and type of invasive (re-)interventions, admission to the Intensive Care Unit (ICU), length of ICU stay, length of hospital stay, readmission rate, number of patients receiving adjuvant chemotherapy at 90 day follow up, duration of postoperative pancreatic fistula (time to removal of the last abdominal drain or completion of pancreatectomy), success of implementation (i.e. based on number and timing of abdominal CT scans and proportion of patients’ days in which the algorithm was not followed). Daily data on the incidence and duration of SIRS, sepsis and organ failure (according to the definitions in Table 1 and according to Sequential Organ Failure Assessment (SOFA) and the Multiple Organ Dysfunction Score (MODS)) are also collected [27–29]. In addition, we aim to evaluate the impact on quality of life, total direct and indirect costs and budget impact (see “Economic evaluation”).

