### Statistical analysis

For statistical analysis, outcomes of all patients undergoing pancreatic resection before implementation of the algorithm (i.e. current practice) will be compared to outcomes of all patients undergoing pancreatic resection after implementation of the algorithm (i.e. best practice). The date of pancreatic resection will determine the study phase in which a patient will be analyzed. The primary analysis will be on an intention-to-treat basis according to the planned date of cross-over to care according to the algorithm. Data from patients in the wash-in period will be excluded from the primary analysis. Secondary analyses include a per-protocol analysis in which we will compare patients who receive care according to the algorithm (i.e. all resections after first implementation presentation at a center, including patients undergoing pancreatic resection in the wash-in period) to patients undergoing pancreatic resection before cross-over. When appropriate, 95% confidence intervals will be calculated. In all analyses a two-sided value of alpha of 0.05 will be used to denote statistical significance.

Missing baseline data will be imputed using multiple imputation techniques. The primary analysis will be performed using the multiple imputed data. A complete case analysis will be performed to check for inconsistencies. Baseline data will be analyzed and reported using standard descriptive statistics. The chi-square or Fisher’s exact test is used to compare categorical variables as appropriate. Parametric continuous variables are presented as mean with standard deviation (SD) and are compared using Student’s *t* test. Non-parametric continuous variables are presented as median with interquartile range (IQR) and are compared using the Mann-Whitney *U* test.

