The primary endpoint (i.e. composite of post-pancreatectomy bleeding, new-onset organ failure and death) is a binary variable that will be analyzed using mixed-effects logistic regression analysis. Secondary endpoints will be analyzed using crude and adjusted mixed-effects logistic regression analysis (for binary outcomes) or mixed-effects linear regression analysis (for continuous outcomes). Crude analysis will include a random intercept and random slope at the level of the hospital to adjust for the design, and no other covariates. Adjusted analysis will additionally include the following covariates: calendar time and time since cross-over as a continuous variable, predictors for postoperative pancreatic fistula (i.e. soft pancreatic texture, small-diameter pancreatic duct, increasing blood loss during pancreatic resection and underlying disease that is *not* pancreatitis or pancreatic adenocarcinoma [33]) and predictors for the primary endpoint (i.e. male gender, increasing age, American Society of Anesthesiologists (ASA) classification > 2, index pancreatic resection pancreatoduodenectomy; based on multivariable logistic regression analysis as presented in Table 4). Relevant model assumptions (such as distribution of residuals) will be checked for all models; if deviations from the analysis plan are required this will be described. Crude and adjusted odds ratios with 95% confidence interval and *p* value will be reported.

**Table 4 Tab4:** Factors associated with the composite primary endpoint in 1686 patients undergoing pancreatic resection in the Dutch Pancreatic Cancer Audit

Outcome	Univariable		Multivariable	
	OR (95% CI)	*P* value	OR (95% CI)	*P* value
Male gender	1.64 (1.20–2.23)	0.002	1.64 (1.19–2.27)	0.002
Age	1.02 (1.01–1.04)	0.003	1.02 (1.00–1.03)	0.04
BMI	1.00 (1.00–1.01)	0.52		
ECOG performance score		0.17		
2 vs. 1	1.29 (0.92–1.79)	0.14		
3 vs. 1	1.59 (0.95–2.66)	0.08		
4 vs. 1	0.44 (0.06–3.33)	0.43		
ASA classification (3 and 4 vs. 1 and 2)	1.87 (1.33–2.61)	< 0.001	1.79 (1.26–2.53)	0.001
Preoperative additional nutrition		0.05		
Oral vs. none	0.98 (0.70–1.38)	0.91		
Via nasogastric tube vs. none	1.74 (0.92–3.28)	0.90		
Via TPN vs. none	4.04 (1.17–14.02)	0.03		
Preoperative biliary drainage	0.97 (0.71–1.32)	0.82		
Distal pancreatectomy vs. pancreatoduodenectomy	0.50 (0.31–0.79)	0.003	0.58 (0.36–0.94)	0.03
Texture pancreas (hard/firm vs. soft/normal)	1.22 (0.86–1.73)	0.26		

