### Subgroup and sensitivity analyses

Analyses will be performed both on the group of patients undergoing pancreatoduodenectomy and on the entire group of all patients undergoing pancreatic resection. Additional subgroup analyses will be performed based on adherence to the study protocol (i.e. proportion of patients’ days in which the algorithm is followed), hospital volume (> 45 vs. ≤ 45 pancreatic resections a year), pathologic nature of disease (malignant disease), in patients with postoperative pancreatic fistula and in patients with a high risk of pancreatic fistula [34].

A sensitivity analysis will be performed to evaluate the impact on outcomes related to postoperative pancreatic fistula. To this aim, the adjudication will be asked if an outcome was related to postoperative pancreatic fistula and if this outcome could have been prevented by adherence to the algorithm. Two separate analyses will be performed on the Comprehensive Complication Index: one analysis including all complications and one adjusted analysis, in which interventions imposed by the algorithm (e.g. minimal invasive catheter drainage and use of antibiotic management for abdominal sepsis) will not be included in the calculation. A sensitivity analysis will be performed to evaluate the success of implementation. Centers will be divided into equally sized clusters based on the percentage of additional abdominal CT scans per patient after implementation, as compared with before implementation. Separate analysis will be performed for each group.

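### The adjuvant-chemotherapy endpoint is compared in all resected patients, including those with non-malignant disease who cannot receive it; this dilutes any effect by an amount that depends on an eligible share the protocol does not give

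*Protocol article*

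**What the plan says.** Outcomes lists, among the secondary endpoints, the "number of patients receiving adjuvant chemotherapy at 90 day follow up". The last paragraph of Background names the number of patients receiving chemotherapy among the outcomes on which the trial will test superiority.

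Three sections fix the population:
- Participants: "All patients undergoing all types of pancreatic resection in these centers are identified and will be recruited in this trial", and "There are no exclusion criteria for centers or patients (i.e. nationwide complete enumeration".
- Statistical analysis: "outcomes of all patients undergoing pancreatic resection before implementation of the algorithm (i.e. current practice) will be compared" with those of all patients resected afterwards.
- Subgroup and sensitivity analyses: analyses are done "both on the group of patients undergoing pancreatoduodenectomy and on the entire group of all patients undergoing pancreatic resection".

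The rationale is in Background: "patients with a complicated postoperative course are often unfit to receive adjuvant chemotherapy". Economic evaluation repeats it as a route to better survival.

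Two provisions bear on case mix. The adjusted model includes calendar time and a disease covariate that separates "disease that is *not* pancreatitis or pancreatic adenocarcinoma" from the rest. The additional subgroups include one by "pathologic nature of disease (malignant disease), in patients with postoperative pancreatic fistula". The crude model has hospital random effects and no covariates.

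**The concern.** The mechanism behind this endpoint can act only in patients who have a reason to receive adjuvant chemotherapy. Patients resected for pancreatitis or other non-malignant disease are enrolled and can never be recipients, whatever their postoperative course. Their inclusion shrinks the absolute difference in proportion to the eligible share, while the standard error falls much less.

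It also makes the crude proportion depend on the mix of diagnoses. If that mix changes over the trial, the crude comparison moves without any change in care.

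At stake is the precision and clarity of a stated secondary aim. The primary endpoint is not involved.

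**Working it through.** **Inputs from the protocol.** At least 1600 resections (Abstract); 17 centers, 18 periods, ICC 0.009 (Sample size calculation). That ICC was estimated for the planning of the primary endpoint; using it here is an assumption. The eligible share *e* and the chemotherapy rate are not given, so both are assumed and varied.

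**Check of the method on the plan's own figure.** For 13.8% versus 6.9%, two-sided alpha 0.05 and power 0.80, the two-proportion formula gives 305 per arm, 610 in total. With k = 17 steps, n = 3.9 per center and step, and rho = 0.009, the stepped-wedge design effect is

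[(1 + rho(kn + n − 1)) / (1 + rho(0.5kn + n − 1))] × [3(1 − rho) / (2(k − 1/k))] = (1.6228 / 1.3245) × 0.08774 = 0.1075.

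The required total is 610 × 0.1075 × 18 = 1180, against 1186 stated. Hussey-Hughes power at N = 1186 (pooled variance) is 0.80. The plan's figure is reproduced, so the same power function can be used for the chemotherapy endpoint.

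**Power formula.** With I = 17, T = 18, m = N/306, mean rate p̄, s² = (1 − rho)p̄(1 − p̄)/m and t² = rho·p̄(1 − p̄):

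Var = I·s²(s² + T·t²) / [(IU − W)s² + (U² + ITU − TW − IV)t²].

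Here U = 153 and W = V = 1785, so the bracketed coefficients are 816 and 7752. Power = Φ(|difference|/√Var − 1.96).

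**Dilution.** Ineligible patients have rate 0. In all patients the rates are *e* × 50% and *e* × 60%, with N = 1600. In eligible patients they are 50% and 60%, with N = 1600 × *e*.

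| Eligible share | Rates, all patients | Power, all | Power, eligible only |
|---|---|---|---|
| 90% | 45% vs 54% | 0.72 | 0.77 |
| 80% | 40% vs 48% | 0.62 | 0.73 |
| 60% | 30% vs 36% | 0.43 | 0.62 |

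Worked row at 60%:
- All patients: SE = 0.0334, so 0.06/0.0334 − 1.96 = −0.16 and power is 0.43.
- Eligible only (N = 960): SE = 0.0440, so 0.10/0.0440 − 1.96 = 0.31 and power is 0.62.

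Other assumed effects give the same direction. For 60% to 70%, power is 0.62 versus 0.77 at 80% eligible and 0.41 versus 0.66 at 60%. For 50% to 65% at 60% eligible, it is 0.76 versus 0.93.

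**Case-mix drift with no true effect.** Number the periods 0 to 17, with 17 − j centers still in control in period j. Control center-periods then have mean time 816/153 = 5.33, or 0.31 of the trial. Intervention center-periods have mean 1785/153 = 11.67, or 0.69. Suppose the eligible share falls linearly from 55% to 50% and 60% of eligible patients receive chemotherapy.
- Eligible shares are 55 − 5 × 0.31 = 53.4% (control) and 55 − 5 × 0.69 = 51.6% (intervention).
- Receipt is 32.1% versus 30.9%, a crude odds ratio of about 0.95.
- A purely within-hospital comparison spans half the trial, so the share shifts by 2.5 points (53.75% to 51.25%). Receipt is then 32.25% versus 30.75%, an odds ratio of about 0.93.

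**Whether the plan's safeguards remove this.** The disease covariate puts pancreatitis and adenocarcinoma in the same level, so it does not separate patients who can receive chemotherapy from those who cannot. Calendar time in the adjusted model addresses smooth drift but leaves the certain non-recipients in the denominator.

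**The case against.** The endpoint is one item in a long list and carries no denominator of its own. In a condensed article that detail could be left to the analysis plan. This would decide the matter if the article were silent on the population, but Participants, Statistical analysis, and Subgroup and sensitivity analyses all state it, and followed as written they include non-malignant disease.

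A malignant-disease subgroup is planned and is not confined to the primary endpoint. This stands in part: something close to the right analysis may be produced. But it is an additional analysis, it is not tied to this endpoint, and malignant disease is not the same as a diagnosis for which adjuvant chemotherapy is given.

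Three stronger readings are tempting and not supported:
- *The endpoint loses much of its power.* The documents give neither the eligible share nor the chemotherapy rate, and at 90% eligible the loss is about 5 points. A calculation on 593 per phase would also mislead, because that is half of 1186, the pancreatoduodenectomy target, not half of all resections.
- *Case-mix shifts could pass for a sizeable effect.* Applying a whole fall from 55% to 50% between phases gives an odds ratio of 0.87 (33% versus 30%). Control and intervention periods overlap in calendar time, so a linear drift of that size gives about 0.95, and the adjusted model includes calendar time.
- *The 90-day wording drops patients who started and stopped early.* Outcomes states that all outcomes are assessed up to 90 days, which supports a cumulative reading.

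**Conclusion.** The point holds as a mismatch between a secondary endpoint and its stated population. For an assumed 10-point effect from 50% to 60%, including patients who cannot receive chemotherapy costs about 5 points of power at 90% eligible, 11 at 80% and 19 at 60%. These figures rest on an assumed eligible share, assumed rates, an ICC borrowed from the primary endpoint's planning, equal cluster sizes and a model with period effects. They show the scale of the loss and do not predict the trial's power.

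Exposure of the crude model to case-mix drift is mild, and the adjusted model covers it in part. Dilution is not covered by either model. The primary analysis and its conclusion are unaffected.

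**What to change.** Make the main analysis of this endpoint the proportion of patients who start adjuvant chemotherapy within 90 days of resection, among those whose final pathology is on a prespecified list of diagnoses (at least pancreatic adenocarcinoma). Define membership by pathology alone, irrespective of the postoperative course, so that recovery does not select the denominator and no unblinded judgment of suitability enters. Count patients who die or become unfit before starting as not started. Keep the all-patient number as a descriptive figure.

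The cost is a sentence and a diagnosis list. Pathology is already needed for the disease covariate and the malignant-disease subgroup, so no new data are required. The downside is a smaller denominator; in the calculations above, power is still higher than in all patients at every eligible share shown.

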**Fig. 1 Fig1:**
[figure not shown]
Standard Protocol Items: Recommendation for Interventional Trials (SPIRIT) schedule of enrollment, interventions and assessments

The stepped-wedge, cluster-randomized trial is a form of cross-over design with unidirectional cross-over (from control to intervention phase) at different time points for each cluster (Fig. 2). Each cluster will contain one center. Randomization will determine the order in which each center will undergo the transition [15, 16]. In the first timeframe, all centers will deliver current practice (i.e. control). In the second timeframe, the center in the first cluster will start with algorithm-based best practice (i.e. intervention), while all other centers will still deliver current practice. In the third timeframe, the second cluster will implement the algorithm. Following this approach, we proceed until all centers have stepped over to the algorithm. In the last timeframe, all centers will deliver treatment according to the algorithm. Each cluster will contain one center; therefore, the number of sequences is equal to the number of participating centers and this will be 17. To ensure adequate implementation of the algorithm, a wash-in period was designed in which clinicians in the center will be intensively trained by the research team on the algorithm. To avoid contamination of centers still in the current-practice phase, local clinicians will only have access to the algorithm after cross-over to care according to the algorithm.

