A schematic overview of the multilevel algorithm is provided in Fig. 3. It is based on daily standardized evaluation of all patients undergoing pancreatic resection from postoperative day 3 to discharge up to a maximum of 14 days. The algorithm will provide daily advice on three decision levels: indication for abdominal computed tomography (CT) scan (Fig. 4); indication for (invasive) intervention (i.e. minimally invasive percutaneous drainage and/or antibiotic treatment) based on evaluation of the abdominal CT scan (Fig. 5) and indication for removal of abdominal drain(s) (Fig. 6). The algorithm includes clinical data from physical examination and biochemical tests (i.e. systemic inflammatory response syndrome (SIRS), C-Reactive protein (CRP), white blood cell count (WBC), drain production including amylase content and a daily consult from a pancreatic surgeon). At predefined, evidence-based cutoff points (Fig. 4), an abdominal contrast-enhanced CT scan and possibly subsequent minimally invasive intervention should be performed or antibiotic treatment should be started (Fig. 5). Each CT scan will be evaluated according to predefined criteria (Fig. 5) to assess whether there is suspicion of a pancreatic fistula and whether there is an indication for minimally invasive percutaneous catheter drainage. In the case of no clinical improvement within 48 h after the last CT scan, a further CT scan should be performed to assess the indication for and possibility of (additional invasive) intervention. The indication to remove abdominal drains will be evaluated daily starting on postoperative day 3, for as long as there are abdominal drains in place (Fig. 6). The interpretation of the algorithm, the rationale behind the different proposed cutoff points and the proposed management of bleeding or hepaticojejunostomy leakage is provided in Additional file 1: Appendix 2. Since we propose an intervention of structured use of diagnostic and invasive interventions that are already used in daily practice, no additional harms to patients are introduced in this study.

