Data from the Dutch Pancreatic Cancer Audit (2014–2015). Presented are the outcomes of univariable and multivariable logistic regression model showing gender, age, American Society of Anesthesiologists (ASA) classification and type of index resection are independently associated with the occurrence of the composite primary endpoint

*OR* odds ratio, *BMI* body mass index, *ECOG* Eastern Cooperative Oncology Group, *TPN* total parental nutrition

Length of hospital stay will be calculated from the date of the index pancreatic resection and will be analyzed using mixed-effects Cox proportional hazards regression, using discharge alive as the outcome event. Patients who die during the index hospitalization will be censored at the day of death. Length of ICU stay and time to resolution of pancreatic fistula (i.e. time to removal of the last abdominal drain or completion of pancreatectomy) will be analyzed using a zero-inflated negative binominal regression model.

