Leakage of pancreatic enzymes causes a local inflammatory response and thereby excretion of acute-phase enzymes like C-reactive protein, release of white blood cells and clinical signs of inflammation like fever, tachycardia and tachypnea [45, 46]. Amylase levels might be elevated when measured in abdominal drain fluid [10]. The abdominal drain might, however, not be in an adequate position to drain pancreatic leakage. In addition, abdominal drains are becoming more frequently omitted at the time of pancreatic resection or are removed in the early postoperative phase [47]. In these patients, signs of inflammation are the only early signs of postoperative pancreatic fistula. These signs are, however, nonspecific and often not recognized as potential pancreatic leakage, especially in centers where only a few patients with pancreatic fistula are seen annually [45]. We believe, however, that in these patients with a high risk of life-threatening complications, early abdominal CT should be performed and peripancreatic fluid collections should be managed aggressively with percutaneous drainage in patients showing signs of systemic inflammation [9, 48, 49]. This might result in an increased use of abdominal imaging and percutaneous catheter drainage procedures in the entire study population, with the intention of reducing severe bleeding, organ failure or mortality in a subset of patients. The outcomes of this trail will provide more insight into the “number needed to scan” or “number needed to drain” and the cost-effectiveness of intensified postoperative monitoring.

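### Fistula duration ends at removal of the last drain, which the algorithm advises on only after cross-over, so a between-phase difference cannot be read as faster or slower fistula resolution

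*Protocol article*

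**What the plan says.** The Outcomes section of the protocol article lists, among the secondary endpoints, "duration of postoperative pancreatic fistula (time to removal of the last abdominal drain or completion of pancreatectomy". The Statistical analysis section uses the same operational definition under a different name, "time to resolution of pancreatic fistula (i.e. time to removal of the last abdominal drain or completion of pancreatectomy", and assigns it a zero-inflated negative binomial model.

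The Intervention section describes what changes at cross-over: "The algorithm will provide daily advice on three decision levels". These are the indication for a CT scan, the indication for drainage or antibiotics, and the "indication for removal of abdominal drain(s) (Fig. 6"). On the last of these it adds: "The indication to remove abdominal drains will be evaluated daily starting on postoperative day 3, for as long as there are abdominal drains in place".

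The Trial design section (text under Fig. 1) keeps this rule out of the control phase: "local clinicians will only have access to the algorithm after cross-over to care according to the algorithm". The Discussion acknowledges that the strategy may lead to more percutaneous catheter drainage across the whole study population.

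**The concern.** The event that stops the clock is itself a component of the intervention. After cross-over, removal of the last drain is guided by a study rule that is consulted daily; before cross-over it follows each center's own practice. The algorithm also guides the placement of new percutaneous drains, and each added drain can postpone the last removal. The measured interval can therefore change between phases while the fistulas themselves last exactly as long as before.

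The Background section says that the trial will assess superiority on other clinical outcomes. Fistula duration is listed among those outcomes, as an item separate from success of implementation. At stake is whether a between-phase difference in this endpoint may be reported as fistulas resolving sooner or later under the algorithm.

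**Working it through.** The plan gives no figure for drain days, so there is nothing to reproduce. The check sets the relevant statements side by side and then uses a small illustration.

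**The statements compared**

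| Element | Before cross-over | After cross-over | Source |
|---|---|---|---|
| Decision to remove a drain | Current local practice, no access to the algorithm | Daily advice from the algorithm from day 3 | Trial design; Intervention |
| Decision to place a percutaneous drain | Current local practice | Algorithm advice after CT; use may rise | Intervention; Discussion |
| End of the endpoint | Last drain out, or completion pancreatectomy | The same | Outcomes; Statistical analysis |
| Clinicians aware of phase | Yes | Yes | Randomization, blinding and treatment allocation |

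The definition is identical in both phases, but the process that produces the stopping event is not. Blinded adjudication does not help, because it is stated for the primary outcome and drains are removed by clinicians who know the phase.

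The plan recognises a similar difficulty elsewhere. Under Subgroup and sensitivity analyses, the Comprehensive Complication Index is to be analysed a second time without the procedures that the algorithm itself triggers. No counterpart is stated for fistula duration.

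**Illustration (every input is an assumption)**

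Let measured duration = true duration F + lag L from the end of the leak to drain removal. Take F as lognormal with median m = 10 or 20 days and log-SD 0.7, and L with a mean of 1, 3 or 5 days. Then:

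- mean of F = m × exp(0.7²/2) = m × exp(0.245) = m × 1.2776, which is 12.78 days (m = 10) or 25.55 days (m = 20);
- ratio of means = (r × mean F + intervention lag) / (mean F + control lag), where r is the true ratio of durations.

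| True ratio r | Mean lag, control → intervention | m = 10 | m = 20 |
|---|---|---|---|
| 1.0 | 3 → 1 | 13.78/15.78 = 0.87 | 26.55/28.55 = 0.93 |
| 1.0 | 5 → 1 | 13.78/17.78 = 0.77 | 26.55/30.55 = 0.87 |
| 1.0 | 3 → 5 | 17.78/15.78 = 1.13 | 30.55/28.55 = 1.07 |
| 0.8 | 3 → 3 | 13.22/15.78 = 0.84 | 23.44/28.55 = 0.82 |
| 0.8 | 3 → 5 | 15.22/15.78 = 0.96 | 25.44/28.55 = 0.89 |

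The first three rows show an apparent effect, in either direction, with no change in the leak. The fourth row shows that the endpoint does respond to a real 20% shortening when lags are equal. The fifth shows such a shortening partly or almost wholly hidden.

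Placement acts in the same way. If extra percutaneous drains lengthened the time to last removal by 10 to 20 days in a further 10% of patients (again an assumption), the mean would rise by 0.10 × 10 = 1 day to 0.10 × 20 = 2 days.

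**The case against.** The strongest reply is that the trial compares whole care strategies, drain removal included, so time with a drain under each strategy is a legitimate outcome of the package. The definition is printed beside the label both times, so a careful reader is not misled. The stated hypothesis concerns major complications and death, and nowhere does the article predict that fistulas will resolve faster. Reinterventions are already listed by number, timing and type. All of this stands, and it is why the remedy concerns labelling and interpretation and does not call for dropping the endpoint. It does not rescue the reading as fistula resolution, which is the name used in the Statistical analysis section.

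On completion pancreatectomy, stopping a duration clock when the leaking remnant is removed is coherent. It is less coherent to call that resolution, because the Discussion reserves relaparotomy as a salvage option. An early salvage operation would then count as a short duration.

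Two stronger readings are tempting, and the documents do not support them:

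- A reader might infer that the endpoint measures only the removal rule. The algorithm's inputs include drain output and drain amylase, both markers of the leak; its output is described as advice; and departures from it are expected and measured. Fig. 6 is not shown, so how closely the rule follows the end of the leak cannot be judged.
- A reader might infer, from the remark that "abdominal drains are becoming more frequently omitted at the time of pancreatic resection or are removed in the early postoperative phase" and from the zero-inflated model, that a patient with a fistula but no drain is scored as zero days. No such coding is stated. Table 1 defines fistula by amylase in drain fluid, so a patient who never has a drain would not meet that definition, and patients without a fistula are an obvious source of zeros.

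**Conclusion.** The concern holds as one of confounding. The endpoint carries information on leak duration, but a between-phase difference also reflects different drain removal and placement practice, and the two cannot be separated from this endpoint alone. It therefore cannot support a claim that fistulas resolve faster or slower under the algorithm.

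The documents do not allow the direction or the size of the distortion to be estimated. The ratios of 0.77 to 1.13 rest wholly on assumed durations and lags. They show only that the artefact could be as large as a real 20% shortening (0.82 to 0.84 with equal lags). The point concerns one secondary endpoint; the primary endpoint and the sample size are not touched.

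**What to change.** - Label the endpoint time to last abdominal drain removal in both the Outcomes and the Statistical analysis sections, and drop the word resolution.
- Report it as a process measure of the care strategy, next to the number and timing of CT scans and reinterventions.
- State that no superiority claim on fistula resolution will be drawn from it.
- Report completion pancreatectomy as a separate event and do not count it as resolution.

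This is a change of wording in the endpoint list and the analysis text and needs no new data. The cost is one fewer clinical efficacy claim among the secondary endpoints. Nothing here proposes when a drain should be removed or placed.
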